### Sample size

Since this study is not testing a statistical hypothesis, but rather exploratory, it is decided to proceed with the minimum number of subjects empirically required within the limit that satisfies the purpose of the study. In general, it should be considered that such exploratory research is usually conducted with around 50 people. Most high-risk pregnant women do not want to visit the hospital after childbirth, so when obtaining consent in advance, patients who have actively consented to long-term observation should be registered. Therefore, it was determined that 12-month observation data could be collected from 150 subjects when about 300 subjects were recruited by calculating the dropout rate as about 50%. Separately, this study checked the health of mothers and newborns before and after pregnancy and considered that most complications such as gestational diabetes occurred within 2 years after childbirth. Accordingly, this study is continuously necessary for a total of 3 years, about 1 year including the entire period of pregnancy, and 2 years to confirm the occurrence of complications and childbirth results as a follow-up. Therefore, about 150 women will receive relevant clinical data every year, and 500 mothers in total will be selected as target subjects.

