### Outcome measure

Table 3 shows the intervention and control groups measured item results, and the same items will be measured after the 6-week study participation period. Primary measurements will include weight, blood pressure, blood sugar and health literacy, and physical and obstetric characteristics. In addition, character, exercise and nutritional information on basic demographic characteristics and basic psychological state will be collected. For the primary measurement, the same information will be collected for both the primary and final results for comparison with the final result.

**Table 3 Tab3:** Outcome measure items

1	Weight, blood pressure, blood sugar measurement
2	Health information literacy
3	Physical and obstetric characteristics (including height, weight, gestational age, date of birth, etc.)
4	Basic demographic characteristics (spouse, marital status, economic status, etc.)
5	Basic psychological status (prenatal-postpartum depression questionnaire, high-risk-related trauma questionnaire, anxiety, and psychological state)
6	International Physical Activity and Exercise Questionnaire (IPAQ)
7	Nutrition and Dietary Questionnaire
8	Newborn information data (weight, head circumference, pregnancy method, birth period, etc.) (after 6 weeks/in case of delivery)
9	Questions for high-risk mothers
10	Smartphone app evaluation questionnaire (only intervention group)
11	App usage effect confirmation questionnaire (only intervention group)
12	Self-report (only intervention group)

Items 1 to 9 in Table 3 are for the intervention and control groups measurement. Item 1 measures body weight, blood pressure, and blood sugar daily during the study period. The amount of change from the start to the end of the study will be evaluated. Item 9 is about high-risk mothers and asks them to check for the diseases that apply to them, such as gestational hypertension, gestational diabetes, and prenatal-postpartum depression. This item will be completed at the beginning and end of the study. When the study is over, it will also be checked whether the disease is maintained. This can help with the prevalence and maintenance of healthcare-related diseases.

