### Statistical analysis

This study will compare the outcomes between the two groups using IBM SPSS software for statistical analysis. For this purpose, descriptive statistics and correlation analysis of each group are performed, and a paired sample T-TEST of two groups is performed, so that comparative analysis can be performed. In addition, pre-post-group comparison analysis will be conducted, especially for both groups, from the first outcome to the final outcome. Hierarchical and stepwise regression analyzes will be conducted to determine the impact of each item to look at changes in health behavior as the end result.

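### The week-6 value may go missing depending on delivery: the plan expects reluctance to attend after childbirth, does not say how delivered women are measured, and names tests that use only complete pairs

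*Protocol article*

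**What the plan says.** Four parts of the protocol article bear on this.

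- **Sample size.** The authors state that "Most high-risk pregnant women do not want to visit the hospital after childbirth". Their response is that "patients who have actively consented to long-term observation should be registered". They then calculate that "12-month observation data could be collected from 150 subjects when about 300 subjects were recruited by calculating the dropout rate as about 50" per cent.
- **Outcome measure.** For both arms, "the same items will be measured after the 6-week study participation period". Item 1 is evaluated as change from start to end, and "Item 1 measures body weight, blood pressure, and blood sugar daily during the study period". The newborn item in Table 3 is timed "after 6 weeks/in case of delivery", so deliveries by the end of participation are foreseen.
- **Statistical analysis.** The article says that "a paired sample T-TEST of two groups is performed", together with pre-post comparisons in both groups.
- **Enrollment and eligibility, Intervention.** All participants receive a scale, a blood pressure device and a glucose device. Automatic transfer of readings is described only into the app, which only the intervention arm downloads. Women diagnosed during or after pregnancy are eligible, and no gestational-age limit is given.

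**The concern.** The authors name childbirth as a reason for not wanting to attend. The week-6 time point can fall before or after childbirth, and a paired test leaves out any woman without the second value. If women who deliver are less likely to supply that value, the women analysed are not the women randomised. The factor that separates them, delivery, also moves weight and can move blood pressure, blood sugar, activity and mood.

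Two consequences follow. With equal loss in both arms, each arm's pre-post mean leans towards women who are still pregnant. With unequal loss, the arms differ at week 6 in the share already delivered, and that alone produces a difference between arms.

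Unequal loss is plausible. App users' readings arrive automatically, and the app also holds depression and psychological questionnaires. For the control arm the article states no route by which readings reach the study team.

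**Working it through.** **The plan's own figure.** 150 / (1 − 0.50) = 300, which reproduces the 300 recruits in the Sample size section. This 50% applies to 12-month data. It is not used below.

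**Step 1: how many women might deliver within 6 weeks.** The article gives no entry distribution, so this is assumed.
- Entry uniform over weeks 24 to 36, delivery at week 39 or 38: (36 − 33)/12 = 25%, or (36 − 32)/12 = 33%.
- Entry uniform from week g to week 40, delivery at week 40: 6/(40 − g). For g = 12, 20, 24 and 28 this gives 21%, 30%, 37.5% and 50%.

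Women who enter after childbirth cannot deliver in the window, so they lower all these shares.

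**Step 2: how many pairs might be lost.** If half of the delivered women lack a final value (assumed), 25% × 0.5 = 12.5% to 33% × 0.5 = 17% of all women drop out of a paired test. In the wider entry windows, with 50% to 80% of delivered women missing and nobody else, 500 randomised leave 446 to 414 pairs (g = 12) and 375 to 300 pairs (g = 28).

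**Step 3: equal loss.** Assume 37.5% deliver, weight change is −6 kg if delivered and +2 kg if not, and there is no treatment effect.
- All women: 0.375 × (−6) + 0.625 × 2 = −1.0 kg.
- Half of delivered women missing: (0.1875 × (−6) + 0.625 × 2)/0.8125 = +0.15 kg in each arm.

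The pre-post mean changes sign, while the difference between arms stays 0.

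**Step 4: unequal loss.** With share p delivering and retention r of delivered women, the delivered share among those analysed is pr/(1 − p + pr). The spurious difference is the gap in that share multiplied by the shift in weight change due to delivery (assumed 5 to 7.5 kg). The standard error (SE) assumes 250 randomised per arm and a within-status SD of 1.5 kg, plus the mixture variance.

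| Retention of delivered women | p | Delivered share analysed | Gap |
|---|---|---|---|
| 70% vs 40% | 0.25 | 0.175/0.925 = 18.9% vs 0.100/0.850 = 11.8% | 7.2 points |
| 70% vs 40% | 0.33 | 0.231/0.901 = 25.6% vs 0.132/0.802 = 16.5% | 9.2 points |
| 60% vs 50% | 0.25 | 0.150/0.900 = 16.7% vs 0.125/0.875 = 14.3% | 2.4 points |

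- 70% vs 40%: 0.0715 × 5 = 0.36 kg (p = 0.25) up to 0.0918 × 7.5 = 0.69 kg (p = 0.33), or 1.6 to 2.1 SE.
- 60% vs 50%: 0.0238 × 5 = 0.12 kg (p = 0.25) up to 0.23 kg (p = 0.33, 7.5 kg), or 0.5 to 0.7 SE.
- Equal retention: 0.

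The 0.69 kg is not a bound. With the inputs of Step 3 and 80% vs 50% retention, the means are −0.59 and +0.15 kg, a spurious difference of 0.75 kg.

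**The case against.** A reader might infer more than the article supports, in four ways.

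- **That women who deliver will be lost.** The text says they do not want to visit, and it answers this by registering women who agree to long observation. Selective loss is a risk here, not a stated outcome.
- **That half of the women will lack a week-6 value.** The 50% belongs to 12-month observation. No 6-week dropout rate is given or implied.
- **That the week-6 measurement needs a hospital visit.** No site or route is named. Weight, blood pressure and blood sugar are measured daily in both arms with supplied devices, so a woman who delivers in week 5 need not lack these values. Paper is the control arm's information material, not evidence that her data stay on paper. This shifts the weight of the point towards the questionnaires, although weight is the outcome for which a size was worked out.
- **That the comparison between arms is biased.** It is biased by this mechanism only if loss differs by arm. Nor can one say that the bias would favour the app, because the article does not define lower weight as the better result.

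It is also fair to say that rules for missing values may sit in an analysis plan that is not shown, and their absence is not held against the article. What remains is what the article does fix: a time point that ignores delivery, a stated expectation of reluctance after delivery, and a complete-pairs test. Readings that are never collected cannot be recovered by a later analysis plan.

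**Conclusion.** The point stands as a risk. The article's own expectation about attendance, its delivery-blind week-6 time point and its paired tests together allow the final value to go missing in a way related to delivery. The pre-post means would then be distorted even with equal loss, and the comparison between arms would be biased if loss is unequal.

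The size cannot be determined from the article. The range for weight, from 0 at equal retention to about 0.7 kg at 70% versus 40%, rests wholly on assumptions about the entry window, the delivery week, retention, the weight shift and the SD. The upper end needs a 30-point gap in retention, and a 10-point gap gives at most 0.23 kg. The risk deserves a change before enrolment because the remedy is cheap and uses equipment and contact details that the trial already has.

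**What to change.** **Outcome measure section.** State that the week-6 items are obtained from every randomised woman by the same route in both arms, including after delivery, with no hospital visit needed: readings from the home devices already supplied, and questionnaires by telephone, web link or post. Record the delivery date in both arms.

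**Statistical analysis section.** Replace the paired complete-case tests with a between-arm comparison of all randomised women. Use a likelihood-based mixed model of all available readings, adjusted for the baseline value and for gestational age (or postpartum status) at entry. Report missing final values by arm and delivery status.

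If readings stop at delivery, such a model carries the pregnancy trajectory past delivery, so add a sensitivity analysis for these women. For items measured only at start and end the model recovers little, and the collection rule does most of the work.

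**Cost.** Protocol wording, a call or questionnaire link at week 6 for women who would otherwise be lost, and a slightly longer analysis. The small downside is that the final questionnaires are completed remotely.

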### Control arm

Participants assigned to the control group will receive paper guidelines about diseases, appropriate exercise during pregnancy, proper diet and nutrition, and pregnancy and newborn care information.

### Intervention

We will randomize participants to the intervention installed on the app via their smartphone. Mothers using this app measured their weight, blood sugar, and blood pressure every day, and the Bluetooth wearable device automatically entered the values into the app. Through this measured and recorded information, the patient will send an intervention message by push notification according to all pregnancy cycles. The intervention message will be delivered to check the nutritional information and exercise method according to the numerical value, and the mother acquires health information while checking the content. In addition to providing medical information throughout the pregnancy cycle, mothers will also receive a schedule of tests to be performed during pregnancy. By the time the mothers will give birth, they will have healthcare information about newborn care and postpartum disease prevention. With this information, mothers can take healthy precautions that benefit them throughout pregnancy. Furthermore, these healthy behaviors can help prevent diseases in the postpartum period.

### Intervention content

The intervention content will be used in the app consists of evidence-based guidelines [19–24] for mothers and literature search materials. For evidence-based data on gestational hypertension, gestational diabetes, and prenatal-postpartum depression, two obstetricians and gynecologists conducted an Agree-II evaluation to confirm the quality and level of evidence. This item will be decided. In particular, exercise during pregnancy is recommended to maintain stability, according to the RCOG guideline [25]. The items agree on the content of the arbitration, as shown in Table 2 below. In addition, the message will be provided in line with the timing of the pregnancy cycle is a bomb push notification so that the detailed items belonging to the major items will be rotated twice a week to reduce the fatigue of mothers.

**Table 2 Tab2:** Intervention content and push message to offer pregnancy cycle interventions

**Main items**	**Main detail items**	**Intervention message**	**The timing of provision according to the pregnancy cycle**
**Delivery**	Prevention education related to childbirth	Hi, $NAME$! Here are some tips to help you prepare for a healthy birth to meet your upcoming baby!	A week before the scheduled date, after delivery, or can be read when clicked
	Postpartum blood pressure management	Hi, $NAME$! If you are worried about your blood pressure readings after your blood pressure test, read these resources! (Normal value: 120/80 mmHg)	Once a week after delivery, or can be read when clicked
	Postpartum proteinuria care	Hi, $NAME$! If proteinuria is detected as a result of a urine test, read the following materials!	Once a week after delivery, or can be read when clicked
**Medical information**	Management of postpartum hypertension	Hi, $NAME$! Let me tell you how to manage gestational hypertension, how to manage postpartum hypertension, how to manage it, risk factors for recurrence, and information that helps prevent recurrence!	record daily figures and Send Information notification, Can be read when clicked
	Recurrence prevention guide	Hi, $NAME$! Let me give you information that helps prevent recurrence of gestational hypertension and recurrence risk factors!	Can be viewed at click
	Chronic Hypertension Risk and Prevention Factors	Hi, $NAME$! Let me show you the risk factors related to hypertension and the prevention factors of hypertension!	Can be viewed at click
	Relevance to cardiovascular disease	Hi, $NAME$! Here’s a guide to the link between high blood pressure and cardiovascular disease and the long-term risk factors!	Can be viewed at click
	Guide to hospitals with gynecologists stay in	Hi, $NAME$! We will tell you about the basic measures needed in an emergency, as well as nearby emergency centers and obstetrics and gynecology hospitals!	Can be viewed at click
	Prenatal and postpartum depression	Hi, $NAME$! If you are experiencing ups and downs in your emotions and moods due to sudden hormonal changes, read these resources!	record daily figures and Send Information notification, Can be read when clicked
**Newborn care**	Newborn development information	Hi, $NAME$! How well is my baby growing? Find out how your baby’s average body changes by week with following data!	A week before the scheduled date, after delivery, or can be read when clicked
	Newborn health care and caring	Hi, $NAME$! What does our baby eat, how much it grows, how does it need to be washed? Find out how to manage newborn health through the following data!	A week before the scheduled date, after delivery, or can be read when clicked
	Newborn crisis management	Hi, $NAME$! If our baby suddenly gets sick or has strange symptoms, how do we deal with it? Find out how to deal with the crisis through the following data!	A week before the scheduled date, after delivery, or can be read when clicked
**Diet and nutrition**	Basic information on diet and eating habits	Hi, $NAME$! What kind of eating habits should have to take care of your health? Learn about your eating habits that can improve your health through the following data!	After participating in the study, detailed items below diet and nutrition are sent twice a week. And can be read when clicked
	Information on salt intake and its dangers	Hi, $NAME$! How much salt should we consume per day? How much sodium is in your diet? Find out with these resources!	After participating in the study, detailed items below diet and nutrition are sent twice a week. And can be read when clicked
	Healthy eating habits	Hi, $NAME$! It is very important to maintain normal blood sugar, blood pressure, and weight through good eating habits. Find out what eating habits are helpful through the following data!	After participating in the study, detailed items below diet and nutrition are sent twice a week. And can be read when clicked
	Nutrition and recommended foods	Hi, $NAME$! You should take enough nutrients during pregnancy. Find out about essential nutrients and food through the following data!	After participating in the study, detailed items below diet and nutrition are sent twice a week. And can be read when clicked
	Nutrient ratio	Hi, $NAME$! Did you know that there are five major nutrients to be consumed during pregnancy? Find out the five nutrients you need from you through the following data!	After participating in the study, detailed items below diet and nutrition are sent twice a week. And can be read when clicked
	Attentional food	Hi, $NAME$! Find out what foods you should be careful about because they are not good for pregnancy!	After participating in the study, detailed items below diet and nutrition are sent twice a week. And can be read when clicked
	Nutritional supplements by gestational period	Hi, $NAME$! What are additional nutritional supplements other than nutritional intake through food, and when should I take them? Find out more about the nutritional supplements you need to take by pregnancy period through the following data!	After participating in the study, detailed items below diet and nutrition are sent twice a week. And can be read when clicked
	Morning sickness management	Hi, $NAME$! What is the occasional morning sickness during pregnancy, and how can it be relieved? Find out how to take care of morning sickness through the following resources	After participating in the study, detailed items below diet and nutrition are sent to the message twice a week. And can be read when clicked
**Exercise and physical activity**	The physical activity guide	Hi, $NAME$! Excessive exercise during pregnancy has a risk of premature birth. Find out about the appropriate amount of physical activity and exercise for mothers through the following resources!	After participating in the study, detailed items below exercise and physical activity are sent to the message twice a week, And can be read when clicked
	Guide to the intensity and type of exercise	Hi, $NAME$! Exercise is necessary for effective weight, blood pressure, and blood sugar management. Find out more about the types and intensity of exercise to help you get pregnant with these resources!	After participating in the study, detailed items below exercise and physical activity are sent to the message twice a week, And can be read when clicked
	Restrictions and precautions for exercise and physical activity	Hi, $NAME$! Exercise is necessary for effective weight, blood pressure, and blood sugar management. Learn more about exercise and physical activity precautions during pregnancy with these resources!	After participating in the study, detailed items below exercise and physical activity are sent to the message twice a week, And can be read when clicked
	The importance of weight management	“Hi, $NAME$! Read our resources on how to change and manage your weight properly for your desired weight management!	After participating in the study, detailed items below exercise and physical activity are sent to the message twice a week, And can be read when clicked
	Information on weight change during pregnancy	“Hi, $NAME$! Find out what is proper weight change during pregnancy and how weight changes for pregnant women in general!	After participating in the study, detailed items below exercise and physical activity are sent to the message twice a week, And can be read when clicked
	Weight management after childbirth	Hi, $NAME$! Read our article on proper weight change and how to manage it for good postpartum weight management!	After participating in the study, detailed items below exercise and physical activity are sent to the message twice a week, And can be read when clicked
	Prenatal and postpartum exercise guide	Hi, $NAME$! Prenatal-postpartum exercise is a great help to your physical and mental health, and is also essential for rapid recovery. Find out the importance, type and recommended amount of prenatal-postpartum exercise!	After participating in the study, detailed items below exercise and physical activity are sent to the message twice a week, And can be read when clicked
**Self-record**	A daily log of your condition during pregnancy	Hi, $NAME$! It’s a self-record for me! Write every day on the subject this week! You don’t have to write long. Just write at least three sentences!	Send a message once a week, or can be read when clicked
**Emergency/urgency management**	Crisis of gestational hypertension	Hi, $NAME$! In the case of gestational hypertension, a hypertensive crisis can strike unexpectedly. Find out what a hypertensive crisis is and how to deal with it with these resources!	Send a message once a week, or can be read when clicked
	Guide on risk blood sugar level	Hi, $NAME$! What is gestational diabetes and what is the blood sugar level that you diagnose as diabetes? Find out the blood sugar levels of gestational diabetes through the following data!	Send a message once a week, or can be read when clicked
	Guide on depression symptoms and examination	Hi, $NAME$! The hormone changes that occur during pregnancy also affect your mood and feelings. With deep depression or negative emotions, check your psychological state with the following data!	Send a message once a week, or can be read when clicked
	Hospitals where you can receive information in case of an emergency	Hi, $NAME$! How can you deal with an unexpected crisis during pregnancy? Find out the following data about the possible crisis during pregnancy and how to do it!	Send a message once a week, or can be read when clicked

